## Abstract

**Background:**

There is a lack of firm knowledge regarding sexual problems and fertility-related distress in young adults following a diagnosis with cancer. Establishing such understanding is essential to identify patients in need of specific support and to develop cancer care accordingly. This study protocol describes the Fex-Can Cohort study, a population-based prospective cohort study investigating sexual dysfunction and fertility-related distress in young adults diagnosed with cancer in Sweden. The primary objective of the study is to determine the prevalence and predictors of sexual dysfunction and fertility-related distress following a cancer diagnosis in young adulthood compared to prevalence rates for the general population. Further aims are to investigate the trajectories of these issues over time, the co-existence between sexual dysfunction and fertility-related distress, and the relation between these issues and body image, anxiety and depression, health-related quality of life, self-efficacy related to sexuality and fertility, and fertility-related knowledge.

**Methods:**

Participants in the Fex-Can Cohort will be identified via the Swedish National Quality Registries for Brain Tumors, Breast Cancer, Gynecological Oncology, Lymphoma, and Testicular Cancer. All patients diagnosed at the ages of 18–39, during a period of 18 months, will be invited to participate. Established instruments will be used to measure sexual function (PROMIS SexFS), fertility-related distress (RCAC), body image (BIS), anxiety and depression (HADS), and health-related quality of life (QLQ-C30); Self-efficacy and fertility-related knowledge will be assessed by study-specific measures. The survey will be administered to participants at baseline (approximately 1.5 year after diagnosis) and at 3 and 5 years post-diagnosis. Registry data will be used to collect clinical variables. A comparison group of 2000 young adults will be drawn from the Swedish population register (SPAR) and subsequently approached with the same measures as the cancer group.

**Discussion:**

The study will determine the prevalence and predictors of sexual dysfunction and fertility-related distress in young men and women with cancer. The findings will form a basis for developing interventions to alleviate sexual problems and fertility-related distress in young adults with cancer in the short and long term.

**Trial registration:**

This is an observational cohort study and clinical trial registration was therefore not obtained.

## Background

Cancer affects large groups of young adults, commonly defined as those between 18 to 39 years of age. Globally about one million young adults are diagnosed with cancer yearly, and the corresponding figure in Sweden is approximately 2000 [1, 2]. In addition to being a life-threatening condition, cancer and its treatments may impair several aspects of the general health, including sexual and reproductive functions. Being diagnosed with cancer during young adulthood can thus be particularly distressing by interfering with important life goals, such as establishing intimate relationships and building a family [3].

Previous research has reported that over 40% of young adults with cancer experience sexual problems within the first 2 years following diagnosis [4, 5]. Problems commonly reported by women include reduced sexual desire, vaginal dryness and/or dyspareunia, difficulties in sexual arousal and/or orgasm, and low satisfaction with sex life [6–8]. In men diagnosed with cancer erectile dysfunction, orgasmic difficulties, reduced sexual interest, and low satisfaction with sex life have been reported [9–12]. Sexual problems can be caused by several of the cancers common in the age group and their treatments (i.e., radiation therapy, chemotherapy, endocrine treatment, and surgery), directly or indirectly via physiological, psychological, and interpersonal factors [13, 14]. However, firm knowledge about the mechanisms involved in sexual problems after cancer in young adulthood is not yet established. Previous research has indicated that female gender, higher age, a poor prognosis, and being in a partner relationship predict more sexual problems [4].

Several cancer types and their treatments may cause temporary or permanent infertility or subfertility [15] but fertility potential on an individual level often remains uncertain following cancer in young adulthood [16, 17]. Results indicate that a majority of young women diagnosed with cancer experience fertility-related distress [7, 18], which has been shown to be related to long-term depressive symptoms [19]. In men fertility-related distress following cancer has been studied to a very limited extent. One recent study found that 28% of young men with testicular cancer reported high levels of reproductive concerns approximately 2 years post-diagnosis [11]. In addition, impaired fertility after testicular cancer appears to be related to decreased quality of life and to lower emotional well-being [20, 21]. In recent research, fear of infertility, or knowing that one’s fertility has been compromised, has been associated with negative effects on psychological wellbeing in men diagnosed with various types of cancer [22]. It has also been reported that the threat of infertility is associated with compromised self-esteem, sexuality and body-image in both men and women diagnosed with cancer in young adulthood [11, 16].

Several cancer diagnoses and/or their treatments have potentially negative consequences on fertile ability or sex life, including diagnoses that are common in young adults: brain tumors, breast cancer, cervical cancer, leukemia, lymphoma, ovarian cancer and testicular cancer [1]. Still, research on reproductive and sexual health issues in this group is limited and there is a lack of longitudinal, large-scale studies using validated instruments and reliable comparison data. As a result, knowledge about the prevalence, predictors and trajectory of sexual problems and fertility distress following a cancer diagnosis in young adults is sparse. High quality longitudinal research is needed to advance knowledge necessary to develop cancer care adapted to the needs of this group.

### The Fex-Can project

The project Fertility and Sexuality following Cancer (Fex-Can) includes a cohort study with an embedded randomized controlled trial (RCT) evaluating the effect of a web-based intervention addressing sexual problems and fertility-related distress, see study protocol for the RCT [23]. This intervention was developed and evaluated regarding its feasibility in collaboration with a group of former cancer patients and significant others [24, 25]. The present protocol describes the procedures for the Fex-Can Cohort.

### Objectives

The primary objective of the present study is to determine the prevalence and predictors of sexual dysfunction and fertility-related distress following a cancer diagnosis in young adulthood compared to prevalence rates for the general population. Further aims are to investigate the trajectories of these issues over time, the co-existence between sexual dysfunction and fertility-related distress, and the relation between these issues and body image, anxiety and depression, health-related quality of life, self-efficacy related to sexuality and fertility, and fertility-related knowledge.

## Methods/design

### Study design

The study will have a population-based prospective cohort design, investigating sexual dysfunction and fertility-related distress in young adults diagnosed with cancer over 5 years following diagnosis. The study will also include a cross-sectional assessment of a comparison group, consisting of young adults from the general population.

### Setting

The diagnoses included in the Fex-Can Cohort are selected based on the diseases and/or treatments having potentially negative consequences on fertile ability or sexual life. The incidence of the selected diagnoses in Sweden in 2016 was: brain tumors (*n* = 153), breast cancer (*n* = 350), cervical cancer (*n* = 195), lymphoma (*n* = 132), ovarian cancer (*n* = 39), and testicular cancer (*n* = 220). Individuals diagnosed with leukemia were not included in the Fex-Can Cohort due to an ongoing study concerning fertility issues in this group. Participants will be identified via the Swedish National Quality Registers for Brain Tumors, Breast Cancer, Gynecological Oncology, Lymphoma, and Testicular Cancer. All individuals diagnosed with the selected diagnoses at ages 18–39 during a time period of 18 months will be approached regarding study participation. Data collection will be performed approximately 1.5 years after diagnosis (baseline assessment) and 3 and 5 years after diagnosis. At baseline most participants are expected to have completed first-line treatment and be in the phase of returning to work and studies. In order to time these data assessments to participants’ time of diagnosis, data collections will be performed in three waves (A-C), see Fig. 1. Data for the comparison group will be collected on one occasion.

**Fig. 1 Fig1:**
[figure not shown]
Fex-Can Cohort timeline for data collection of the cancer group

### Recruitment

#### Cancer group

All individuals matching the inclusion criteria (see below) will be approached regarding study participation with a letter outlining the aims and procedures of the study, the voluntary nature of participation, and a postal survey. The survey will be possible to complete on paper or via the web by using a unique participant code. On request, participants may also have the possibility to report their responses by phone. Two reminders will be sent to non-responders. Participants will be offered two cinema tickets (total value of approximately 20 Euro) as incentives for completion of each assessment (baseline and follow-ups).

#### Comparison group

A random sample of 2000 young adults (1000 women and 1000 men) will be drawn from the Swedish population register (SPAR) and approached regarding study participation. The survey will be sent to potential participants, together with a letter with information about the study including the voluntary nature of participation. As for the cancer group, it will be possible to complete the survey on paper, via the web or telephone, and two reminders will be sent to non-responders. The comparison group will be offered the same incentive for participation as the cancer group i.e., two cinema tickets. The comparison group will only be assessed once.

### Eligibility criteria

#### Cancer group

The following inclusion criteria will be used: All individuals in Sweden in ages 18–39 who were diagnosed with brain tumor, breast cancer, cervical cancer, lymphoma, ovarian cancer, or testicular cancer between January 2016 and August 2017. Potential participants without valid address information will be excluded. Furthermore, approached individuals who on their own initiative inform us that they cannot complete the survey due to cognitive impairment, poor health or non-ability to read and/or understand Swedish will also be excluded.

#### Comparison group

For the comparison group the inclusion criteria will be: Age 19–40 (matching the age of the cancer group at baseline assessment) and registered as residents in Sweden. Furthermore, similar to the cancer group, approached individuals who on their own initiative inform us that they cannot complete the survey due to cognitive impairment, poor health or non-ability to read and/or understand Swedish, will be excluded.

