### Sample size

Based on official statistics on cancer incidence in Sweden [2, 40] the eligible population is estimated to approximately 1500 for the inclusion period. Based on our experience of moderate response rates (50–60%) in surveys on sensitive issues in this age group when no incentives were offered [7, 11], we expect the addition of incentives (2 cinema tickets) to result in a larger proportion of responders. An estimated response rate of 70% would result in 1050 participants at baseline. At baseline, a majority of participants (≈80%, *n* = 840) are expected to rate sexual dysfunction or fertility-distress meeting the inclusion criteria for the embedded RCT [23]. Of those invited to the RCT, about half are expected to consent participation (*N* = 420) and these will be excluded for further follow-up in the Fex-Can Cohort, leaving 630 participants for the longitudinal analyses. Attrition in the Fex-Can Cohort due to deaths and other reasons for non-response is estimated to 15% at following assessments, giving an estimated response rate at T2 (*n* = 535) and T3 (*n* = 454). Sample size determination was based on the recommendation to include at least 5 events of the dependent variable of interest (in this case: the primary outcome measures SexFS and RCAC) for each independent variable included in the multivariable logistic regression models [41]. Thus, we estimated that at least 50 events of the dependent variable in the sample are required in order to include up to ten independent variables. Based on the incidence rates of the selected diagnoses, we expected a distribution of approximately 65% women and 35% men in the eligible sample. Previous data of sexual dysfunction and fertility distress in the Swedish setting [7, 11] indicate that the number of events of the dependent variables at baseline is ≈30% for males and ≈60% for females. Based on these numbers, we estimate the sample size to be sufficient for determination of potential predictors for both sexes at all assessment occasions, including the 5-year follow-up. As the Fex-Can Cohort is an observational study, no formal power calculation was conducted.

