### Statistical methods

The study will be reported following the STROBE statement [42] and the SPIRIT-PRO Extension [43]. Descriptive statistics will be used to determine the prevalence of sexual dysfunction and fertility-related distress by diagnosis and sex. These will be presented as means and standard deviations and as percentages of participants above the described cut-offs for these outcomes. Prevalence rates in the cancer group will be compared to prevalence rates in the general population by sex and age group, using Students’ t-test and χ^2^ tests. To determine predictors for sexual dysfunction and fertility-related distress at each assessment we will perform logistic regression models for each primary outcome (SexFS v2-domains and RCAC-dimensions) for the whole group and by sex. Independent variables will include sex (whole group), partner status, parenthood status, child wish (only for RCAC), satisfaction with sex life pre-diagnosis (only for SexFS v2), diagnosis, treatment intensity, body image, anxiety, and depression. Trajectories of these issues over time (T1, T2 and T3) will be analyzed with linear mixed models. Relations between sexual dysfunction and fertility-related distress, and between these issues and our secondary outcomes, will be analyzed with Pearson’s correlation coefficients. Statistical analyses will be performed in collaboration with external statisticians.

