## Discussion

This population-based cohort study aims to determine the prevalence and predictors of sexual dysfunction and fertility-related distress in young adults diagnosed with cancer. The results of the study will increase understanding of the trajectories of sexual dysfunction and fertility-related distress over 5 years following diagnosis.

Our study design includes a large nationwide sample of young adults diagnosed with different cancers and will therefore establish prevalence rates of sexual dysfunction and fertility-related distress over the first 5 years after diagnosis. One of the selected diagnoses, brain tumors, is a cancer often excluded in this kind of research and the group’s sexual dysfunction and fertility-related distress is still largely unknown. Potential participants will be identified through National Quality Registers with excellent coverage, ensuring that all individuals in the age group diagnosed with the selected cancers will be approached [44]. The design also allows for analyses of non-responders and attrition including highly reliable clinical variables. At the baseline assessment some patients may still be on treatment (e.g. lymphoma and breast cancers) and others will have finished their treatment (e.g. testicular cancer). Therefore, treatment status will be described in detail for each diagnosis when reporting prevalence at baseline, and all models will control for current treatment status. While most of the selected patient-reported outcome measures are standardized instruments, it should be noted that the study-specific measures, as well as the shortened versions of the BIS and RCAC for the comparison group, have not been validated. With a young adult comparison group assessed with the same standardized measures it will be possible to determine to what extent the self-rated problems are related to being treated for cancer. As the prevalence of sexual dysfunction in women and men has been reported to vary between countries [45, 46], the use of a comparison group randomized from the total general population in the country is a strength. However, the fact that the comparison group is only assessed at one time point is a limitation as it does not allow comparison of trajectories of these issues over time.

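### The comparison group's age limit of 40 falls one year short of the baseline match claimed for it, and the plan does not say at which assessments the population comparison is made (minor)

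*Protocol article*

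**What the plan says.** The cancer group is defined by age at diagnosis: "All individuals in Sweden in ages 18–39 who were diagnosed with brain tumor" or one of five other cancers (Eligibility criteria, Cancer group). The survey times are in Setting: "Data collection will be performed approximately 1.5 years after diagnosis (baseline assessment) and 3 and 5 years after diagnosis".

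The comparison group is defined by its own age: "Age 19–40 (matching the age of the cancer group at baseline assessment) and registered as residents in Sweden" (Eligibility criteria, Comparison group). It is a random draw of 2000 people, and "The comparison group will only be assessed once" (Recruitment, Comparison group).

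Statistical methods plans the comparison in one sentence: "Prevalence rates in the cancer group will be compared to prevalence rates in the general population by sex and age group". It gives neither the age bands nor the assessment. The Discussion says the study "will therefore establish prevalence rates of sexual dysfunction and fertility-related distress over the first 5 years after diagnosis", and concedes that the fact that "the comparison group is only assessed at one time point is a limitation as it does not allow comparison of trajectories". It does not mention any difference in age range between the groups.

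**The concern.** The comparison group exists to show how much of what patients report goes beyond what people of the same sex and age report anyway. That needs the two groups to cover the same ages when surveyed. The protocol asserts this for baseline, but its own eligibility and timing figures do not give that result at the upper end.

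The gap widens with time, because the cancer group ages 3.5 years between its first and last survey while the comparison group is surveyed only once. If the population comparison were repeated at 3 or 5 years over the full age range, the oldest patients would be set against people aged 40 or younger. The Background reports that earlier research found higher age to predict more sexual problems. If something similar holds in the general population, part of an age difference would be read as a difference due to cancer. Ages that were never sampled cannot be recovered in the analysis; adjustment for age could only extrapolate above 40.

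**Working it through.** **Inputs from the protocol.** Age at diagnosis 18–39 completed years, so exact age 18.0 to just under 40.0 (Eligibility criteria). Surveys at about 1.5, 3 and 5 years (Setting). Comparison group 19–40 completed years, so exact age 19.0 to just under 41.0. Expected participants 1050, 535 and 454 (Sample size).

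**The plan's participant figures.** 1500 × 0.70 = 1050; 1050 × 0.80 = 840; 840 × 0.50 = 420; 1050 − 420 = 630; 630 × 0.85 = 535.5; 535 × 0.85 = 454.75. These agree with the stated 1050, 840, 420, 630, 535 and 454.

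**The plan's age range.** The lower limit reproduces: 18.0 + 1.5 = 19.5, which is 19 in completed years. The upper limit of 40 results only if 1 year is added instead of 1.5 (39 + 1 = 40), or if age 39 is treated as exactly 39.0 (39.0 + 1.5 = 40.5, completed age 40). A person aged 39 can be anywhere up to just under 40.0, and 40.0 + 1.5 = 41.5, which is 41 in completed years.

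**Age ranges at each survey** (exact age at diagnosis plus time since diagnosis):

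| Survey | Exact age | Completed years | Above 40 if age at diagnosis was at least |
|---|---|---|---|
| 1.5 years | 19.5 to <41.5 | 19–41 | 41 − 1.5 = 39.5 |
| 3 years | 21.0 to <43.0 | 21–42 | 41 − 3 = 38 |
| 5 years | 23.0 to <45.0 | 23–44 | 41 − 5 = 36 |

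**Share of patients above the comparison group's limit.** The protocol gives no age distribution, so each row below is an assumption. For a density rising linearly r-fold from age 18 to 40, let F(a) = (a − 18) + (r − 1)(a − 18)²/44. The share at t years is 1 − F(41 − t)/F(40).

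| Assumed age at diagnosis | 1.5 years (n = 1050) | 3 years (n = 535) | 5 years (n = 454) |
|---|---|---|---|
| Uniform | 0.5/22 = 2.3% (24) | 2/22 = 9.1% (49) | 4/22 = 18.2% (83) |
| Rising 3-fold | 3.4% (36) | 13.2% (71) | 25.6% (116) |
| Rising 10-fold | 4.1% (43) | 15.9% (85) | 30.4% (138) |
| Rising from zero at 18 (extreme) | 1 − (21.5/22)² = 4.5% (47) | 1 − (20/22)² = 17.4% (93) | 1 − (18/22)² = 33.1% (150) |

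Baseline timing is only approximate. Under the uniform assumption the baseline share is 1.1% at 1.25 years and 3.4% at 1.75 years; at 1.75 years with a 10-fold rise it is 6.1%.

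**The case against.** The strongest reply is that the group was built for baseline and serves that purpose. The age criterion refers to baseline only. Statistical methods names the time points where it means repeated analysis: predictors are sought at each assessment, and trajectories cover T1 to T3. The sentence on the population comparison has no such phrase. At baseline only patients diagnosed in the last half-year of the age range fall outside, and the timing is approximate. The comparison is by age group, so a 41-year-old would ordinarily sit in a top band with many comparators aged 40 or younger. The Discussion already admits that one assessment limits the use of the follow-up data.

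Most of this stands. A reader might infer that the protocol commits to comparing 3- and 5-year prevalence with the general population, and that the oldest patients have no counterpart in a planned analysis. The documents do not support that. The primary objective states the population comparison without a time point and lists trajectories among the further aims. The Discussion sentence on prevalence over five years concerns the patients and names no comparator. Nor does it follow that an age band would be empty at baseline; that would happen only if a band began at 41, and no bands are given.

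Two things are not answered. The claim of a match is still wrong by one completed year. And the admitted limitation is about trajectories: it neither rules out a cross-sectional comparison at 3 or 5 years nor mentions the ages that would then be missing.

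**Conclusion.** The concern holds in a limited form and is minor.

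- **At baseline** the upper age limit is one completed year (half a year of exact age) short of the match the protocol claims. This concerns about 2% of patients under a uniform age distribution and about 4–5% if incidence rises steeply with age, taking the survey at 1.5 years.
- **At 3 and 5 years** the gap matters only if a population comparison is made there. Then about 9% and 18% of patients under the uniform assumption, and more if incidence rises with age, would be older than anyone in the comparison group.

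The counts also assume that response, transfer to the embedded trial and attrition leave the age distribution unchanged. They measure how many patients lack an age counterpart, not the bias in prevalence. The protocol gives no age gradient for the general population, and the research on age cited in the Background concerns young adults with cancer, so the size of any bias cannot be derived from it.

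**What to change.** 1. Set the comparison group's upper age limit to 41, so that the stated baseline match is true. The same 2000 letters then cover 23 years of age instead of 22, which is 1 − 22/23 = about 4% fewer people per year of age. If the sample has already been drawn, correct the claim of a match instead; that costs one sentence.
2. State in Statistical methods at which assessments prevalence is compared with the general population. If it is baseline only, say so. This costs nothing.
3. If the comparison is also made at 3 or 5 years, restrict it to the ages both groups cover at that survey: from about 21 or 23 up to the comparison group's upper limit. The cost is some precision. With a limit of 40 and uniform ages, about 9% of patients are left out at 3 years and 18% at 5 years, with like shares of the comparison group at its lower end (2 and 4 of 22 years of age). With a limit of 41 the patient losses fall to 1/22 = 4.5% and 3/22 = 13.6%.

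Extending the draw to age 44 is optional and is justified only if a full-range comparison at 5 years is intended. It spreads 2000 people over 26 years of age, which is 1 − 22/26 = about 15% fewer per year, and puts 3/26 = about 12% of them at ages 42–44, which no patient has at baseline.
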